**1.5 Study Objectives.**

Endpoint definitions.

PBD:

≥ 25% progression in size of existing osteolytic lesions (a total growth of at least 10 mm is required in the longest dimension) or vertebral fractures, new osteolytic lesions (at least 10 mm in the longest dimension) or fractures, spontaneous factures, new vertebral compression, new osteolytic lesions needing irradiation therapy or surgery, hypercalcaemia caused by the myeloma (S-Ca-ion > 1,40 mmol/L or in case S-Ca-ion is not measured: S-Calcium adjusted for S-albumin > 2,75 mmol/L), measured in at least two consecutive blood samples.

PBD can be diagnosed on either conventional radiography or low-dose CT. The development however must be defined by comparing the same modality over time. The modality used at the time of randomisation (year 2) will be used as baseline value.

sPBD:

Spontaneous factures, new vertebral compression, new osteolytic lesions needing irradiation therapy or surgery, hypercalcaemia caused by the myeloma (S-Ca-ion > 1,40 mmol/L or in case S-Ca-ion is not measured S-Calcium adjusted for S-albumin > 2,75 mmol/L), measured in at least two consecutive blood samples).

sPBD can be diagnosed on either conventional radiography or low-dose CT. The development however must be defined by comparing the same modality over time. The modality used at the time of randomisation (year 2) will be used as baseline value.

Bone healing:

≥ 25% reduction in the size of osteolytic lesions (a reduction of at least 10 mm in the longest dimension is required), increased sclerosis in the edge of existing lesions, or healing of existing lesions. Bone healing can be diagnosed on either conventional radiography or low-dose CT. The development however must be defined by comparing the same modality over time.

The modality used at the time of randomisation (year 2) will be used as baseline value.

BON:

To diagnose BON the following criteria must be fulfilled

1: Current or previous treatment with a bisphosphonate AND

2: Exposed, necrotic bone in the maxillofacial region that has persisted for more that 8 weeks AND

3: No history of radiation therapy to the jaws [[29](#_ENREF_29)]

No bone disease / Bone disease:

Any radiological signs of bone disease including osteolysis (at least 10 mm), osteopenia, halisteresis, fractures including vertebral compression fractures (these findings are not necessarily equal to a Myeloma Defining Bone Disease Event; which is defined according to the International Myeloma Working Group Consensus Statement Paris 2011). No bone disease / Bone disease can be diagnosed on either conventional radiography or low-dose CT

QoL:

Quality of Life is evaluated using the European Organization for Research and Treatment of Cancer Quality of Life Questionnaire-Core 30 (EORTC QLQ-C30, version 3.0, together with the MY20 multiple myeloma specific supplement.

Primary Endpoint:

To compare the time to PBD from year 2 to year 4 in patients treated with monthly zoledronic acid in two consecutive years compared to patients treated with monthly zoledronic acid in four consecutive years.

Secondary Endpoints:

To compare the incidence of PBD from year 2 to year 4 in patients treated with monthly zoledronic acid in two consecutive years compared to patients treated with monthly zoledronic acid in four consecutive years.

To compare the incidence of sPBD from year 2 to year 4 in patients treated with monthly zoledronic acid in two consecutive years compared to patients treated with monthly zoledronic acid in four consecutive years.

To compare the incidence of bone healing from year 2 to year 4 in patients treated with monthly zoledronic acid in two consecutive years compared to patients treated with monthly zoledronic acid in four consecutive years.

To compare the overall survival from year 2 to year 4 in patients treated with monthly zoledronic acid in two consecutive years compared to patients treated with monthly zoledronic acid in four consecutive years.

To compare the incidence of BON from year 2 to year 4 in patients treated with monthly zoledronic acid in two consecutive years compared to patients treated with monthly zoledronic acid in four consecutive years.

To compare the development in QoL from year 2 to year 4 in patients treated with monthly zoledronic acid in two consecutive years compared to patients treated with monthly zoledronic acid in four consecutive years.

To compare the development in the bone markers CTX-I, PINP, bALP, and TRAP5b from year 2 to year 4 in the patients groups randomised to receive two or four years of treatment with zoledronic acid

To investigate if monthly measurements of the bone markers CTX-I, PINP, bALP, TRAP5b, or the ratios of these can be used to predict the development of PBD from year 2 to year 4.

To investigate the consistency between the finding “no bone disease” when using conventional radiography compared to low-dose CT at diagnosis*.

To investigate if the patients with inconsistency in bone disease status using the different imaging modalities at diagnosis are more likely to progress in bone disease compared to patients diagnosed with “no bone disease” using both modalities*.

To investigate if the three patients groups 1. consistent “no bone disease” 2. inconsistent bone disease 3. consistent “bone disease”, at diagnosis can be identified using the levels of the bone markers CTX-I, PINP, bALP, TRAP5b, ICTP, or the ratio of these.

* Sites may participate in the study without conduction both conventional radiography and low-dose CT.

Amendment: The primary endpoint will not be affected by the amendment. The eight first secondary endpoints will not be affected by the amendment. The last three secondary endpoints will be affected by the amendment, but it is without statistical relevance; see section 1.13

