
Bone imaging in multiple myeloma.

Despite recent advances in imaging techniques, conventional radiography remains the golden standard when evaluating bone disease in MM [[22](#_ENREF_22), [23](#_ENREF_23)]. Presence or absence of osteolytic lesions may define if a patient is ultimately diagnosed with asymptomatic MM (which results in a watch and wait strategy) or active MM (which results in chemotherapeutic treatment). The rational behind this is that patients with osteolytic bone disease rapidly progress to more active disease if left untreated [[24](#_ENREF_24)]. Conventional radiography however, is known to have a low sensitivity since at least 30% of the trabecular bone substance must be lost before osteolytic lesions becomes detectable; likewise areas such as the scapula, the ribs, and the sternum can be difficult to visualise [[22](#_ENREF_22)]. Computed tomography (CT) scanning is superior to conventional radiography in detecting osteolytic lesions, however due to the high radiation exposure it seems inappropriate to use this modality as a screening tool [[25](#_ENREF_25)]. However, because of the advances in radiology it is now possible to design whole body low-dose CT protocols, reducing the radiation exposure from 25.5 mSv to 4.1 mSv (conventional radiography 2.4 mSv) without loosing the visualisation capabilities of the CT [[26](#_ENREF_26)]. Furthermore, low-dose CT is much quicker to perform and less cumbersome for the patients compared to conventional radiography of almost the entire skeleton. Few studies exists which systematically evaluate the use of low dose CT in MM. One prospective study included 39 persons diagnosed with either MM or Monoclonal Gammopathy of Undetermined Significance (MGUS) allowing both initial and restaging scannings to be included [[27](#_ENREF_27)]. A more recent study evaluated retrospectively acquired data from low-dose CT and PET-CT in 51 persons also including both initial and restaging scannings [[28](#_ENREF_28)]. Both studies found low-dose CT to be superior to conventional radiography in detecting bone disease. However, the clinical relevance of these findings remains to be determined.

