**1.4 Study Rational.**

Bone disease in MM is a common disorder leading to pain, possible fractures, hypercalcaemia and a severely reduced quality of life. Treatment with zoledronic acid does not only reduce pain and the risk of SRE but also increase overall survival. Prolonged use however, increases the risk of BON, especially in patients with reduced dental health who undertakes invasive dental procedures. No data are currently available concerning the optimal duration of zoledronic acid treatment, but two years is the most common recommendation since the original studies had a follow-up of approximately 24 months. There are data emerging that indicate that cancellation of treatment results in an increased risk of PBD.

Another completely different alternative when evaluating bone disease in MM is to use biochemical markers. This method is completely without radiation exposure, and it may in the future decide when zoledronic acid should be given and when it should be withheld, thereby reducing the risk of BON without increasing the risk of PBD.

The golden standard when evaluating bone disease in MM is still conventional radiography. Never the less, conventional radiography is a cumbersome and time-consuming investigation for the patient who usually suffers from bone pain. Furthermore, lesions, especially in the axial skeleton, can be difficult to visualise and it has been demonstrated that CT is a more sensitive modality. It is now possible to conduct low-dose CT reducing the radiation exposure to an acceptable level; indicating that it should be the modality of choice. Prospective studies however are still lacking before the precise role of low-dose CT in MM can be defined.

The purpose of this study is threefold. To determine the optimal duration of treatment with zoledronic acid. To investigate if the future role of serum bone markers in MM could be to tailor treatment to the individual patient. Finally, to evaluate if low-dose CT should replace conventional radiography as the golden standard when evaluating bone disease in MM.

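### Two of the three imaging secondary endpoints pool CT-only with radiography-only disease, so they cannot attribute a raised progression risk or a marker pattern to CT-only findings

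*Protocol*

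**What the plan says.** Protocol section 1.5 has three secondary endpoints on imaging at diagnosis.

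- **Agreement.** It begins "To investigate the consistency between the finding" and concerns whether radiography and low-dose CT agree that bone disease is absent.
- **Progression.** It reads "To investigate if the patients with inconsistency in bone disease status using the different imaging modalities at diagnosis are more likely to progress" and continues "in bone disease compared to patients diagnosed with" no bone disease on both methods. The exposed group is anyone whose two readings differ, in either direction.
- **Bone markers.** It asks whether marker levels identify three groups: concordant negative, then "2. inconsistent bone disease 3. consistent" positive.

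Section 1.5 defines bone disease as "Any radiological signs of bone disease including osteolysis (at least 10 mm), osteopenia, halisteresis, fractures including vertebral compression fractures". Either method may establish it, and neither is named as the reference.

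Section 1.4 gives the purpose of the imaging part as "to evaluate if low-dose CT should replace conventional radiography as the golden standard when evaluating bone disease in MM". Section 1.3, on two earlier imaging studies, says "Both studies found low-dose CT to be superior to conventional radiography in detecting bone disease", and adds that the clinical relevance of this is still open. Section 1.13 treats the imaging part as largely descriptive, with each patient as his or her own control, and expects both methods to be used in half of the patients or more.

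**The concern.** Two yes/no readings give four cells; the protocol names three groups. The merged cells are the two discordant ones, and they bear on the replacement question in opposite ways. CT-positive, radiography-negative patients who later progress show what CT adds. Radiography-positive, CT-negative patients who later progress show what CT misses. A raised risk in the combined group fits either account.

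This matters most for the progression endpoint. By the protocol's own account, earlier work already shows that CT detects more, and the open question is whether the extra findings matter clinically. The progression endpoint is the one that links discordance to outcome, and it does so without direction. The marker endpoint inherits the grouping: a marker profile for the middle group could not be read as a profile of CT-only disease.

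**Working it through.** **What there is to reproduce.** The protocol gives no sample size, event count, power or discordance rate for these endpoints, so there is no figure to check. The calculations below are illustrations on stated assumptions.

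**1. Cells against groups**

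| CT | Radiography | Group in the marker endpoint | Role in the progression endpoint |
|---|---|---|---|
| − | − | 1 | reference |
| + | − | 2 | exposed |
| − | + | 2 | exposed |
| + | + | 3 | not used |

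Nothing elsewhere in the protocol separates rows two and three. Section 1.13 refers to discrepancies between the methods, again without direction.

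**2. What the pooled group hides**

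Inputs: 358 planned patients (section 1.13); half imaged with both methods, 358 × 0.5 = 179 (the lower end of the expectation in section 1.13); 20% discordant (assumed), 179 × 0.20 = 35.8, about 36. The number imaged at diagnosis would be lower to the extent that patients enter at year 2 under the amendment.

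| CT-only / radiography-only | Pooled group | Exact McNemar p after splitting |
|---|---|---|
| 32 / 4 | 36 | 2 × 10⁻⁶, more positives on CT |
| 18 / 18 | 36 | 1.0 |
| 4 / 32 | 36 | 2 × 10⁻⁶, more positives on radiography |

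The pooled group is the same size in all three rows, while the direction of disagreement differs completely.

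**3. Effect on the progression comparison**

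Let q be the radiography-only share of the discordant group. Then

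pooled risk = (1 − q) × r(CT-only) + q × r(radiography-only),

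and relative risk = pooled risk ÷ r(double-negative).

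Assume r(double-negative) = 15%. This is scaled from the 7.5% annual incidence of progressive bone disease in section 1.13, 2 × 7.5% = 15% over two years; it is not a figure given for this subgroup. Assume r(CT-only) = 30% and r(radiography-only) = 15%.

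| q | Pooled risk | Relative risk | Excess retained |
|---|---|---|---|
| 0% | 30.00% | 2.00 | 100% |
| 5% | 0.95 × 30 + 0.05 × 15 = 29.25% | 1.95 | 95% |
| 10% | 0.90 × 30 + 0.10 × 15 = 28.50% | 1.90 | 90% |
| 20% | 0.80 × 30 + 0.20 × 15 = 27.00% | 1.80 | 80% |
| 50% | 0.50 × 30 + 0.50 × 15 = 22.50% | 1.50 | 50% |

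**4. Other radiography-only risks**

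- Equal risk in both discordant cells (30% and 30%): the relative risk is 2.00 at every q, so there is no dilution.
- Higher radiography-only risk (CT-only 22.5%, radiography-only 30%, q = 20%): pooled risk = 0.80 × 22.5 + 0.20 × 30 = 24%. The relative risk is 24 ÷ 15 = 1.60, against 22.5 ÷ 15 = 1.50 for CT-only. Pooling inflates.

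**5. Likely size of the radiography-only cell**

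With 35.8 discordant patients, q of 5% to 20% gives 35.8 × 0.05 = 1.8 to 35.8 × 0.20 = 7.2, about 2 to 7 patients.

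**The case against.** Several points on the other side are sound.

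- **Not every imaging endpoint pools.** The agreement endpoint compares the methods directly, and its two-by-two table would show the direction of disagreement. A reader might infer that the whole imaging part loses direction; it does not. That table does not, however, link direction to later progression.
- **The progression endpoint does answer its literal question,** which is whether discordant patients progress more than double-negative ones. What it cannot do is attribute an excess to CT-only findings.
- **The radiography-only group may be very small.** Section 1.3 describes radiography as insensitive and CT as the better detector, so most disagreement should be CT-only. The broad definition of bone disease makes radiography-only positives possible, but it applies equally to both methods and does not show that they are common.
- **Dilution is conditional.** A reader might infer that pooling must hide a real excess in CT-only patients. That requires a non-trivial radiography-only share with lower risk, and the protocol supports neither figure.
- **Splitting does not prove which method is right.** No independent reference standard is planned.
- **A statistical analysis plan, not shown, could tabulate by direction.** That is possible, and the imaging part is descriptive. But the protocol states the three groups itself, so a plan following its wording would pool.

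These points limit the scope and the likely size. They do not remove the mismatch between an undirected group and a directional aim.

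**Conclusion.** The point holds for two of the three imaging endpoints, progression and bone markers. Provided that both kinds of discordance occur, neither can attribute its result to CT-only disease, whatever the risks turn out to be.

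The numerical effect is unknown in size and direction. On the assumed risks it is slight at small radiography-only shares (relative risk 1.95 to 1.80 at 5% to 20%, against 2.00) and substantial only if the two kinds are about equally common (1.50). It vanishes under equal risks and reverses if radiography-only patients fare worse. The primary endpoint, the randomisation and the sample size are untouched. The change is worth making because it is cheap and aligns the endpoints with the stated purpose.

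**What to change.** In section 1.5, define four groups from the two readings at diagnosis: negative on both; CT-positive and radiography-negative; radiography-positive and CT-negative; positive on both. State the progression comparison as CT-positive, radiography-negative patients against those negative on both. Report radiography-positive, CT-negative patients separately, descriptively if they are few. Use the same split in the bone-marker endpoint.

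The cost is the wording of two secondary endpoints and the matching tables, a slightly smaller exposed group, and possibly a very small radiography-only cell. No new data, scans or patients are needed. The split would show which discordant finding precedes progression, and the report should say that this is indirect evidence on the merits of the two methods.

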**1.6 Study Population.**

The study population comprises 358 patients with newly diagnosed symptomatic multiple myeloma. Patients with myeloma are in the Nordic countries treated in haematological clinics The patients will be recruited from participating haematological clinics within the NMSG. All patients will be invited to participate in the protocol if they fulfil the inclusion- and exclusion criteria´s. The patient will be informed of the protocol by the treating physician orally and receive written information in their own language concerning the protocol, according to the ICH-GCP guidelines. If possible, the patient will be encouraged to bring a family member to the information meeting. If needed, the patient will receive time for considerations before deciding if he/she wishes to participate in the protocol. If the patient decides not to participate in the protocol he/she will receive the clinics standard treatment.

Inclusion criteria:

-Symptomatic Multiple Myeloma according to the IMWG criteria, regardless of bone disease status

-Signed Informed Consent

-Age ≥ 18 years

-Remaining life expectancy ≥ 2 years

-Any concurrent anti-myeloma treatment are allowed

Exclusion criteria:

-Previous treatment with bisphosphonate within the last 6 months

-Severely reduced renal function (creatinine clearance <30 mL/min despite fluid replacement)

-Known concurrent malignancy, excluding skin cancer

-Known hypersensitivity to zoledronic acid

-Pregnant or lactating women

-Women of childbearing potential or men engaging in sexual activity with a woman of childbearing potential who refuse to use contraception (safe methods of contraception are considered to be: combined (estrogen and progestogen containing) hormonal contraception associated with inhibition of ovulation, progestogen-only hormonal contraception associated with inhibition of ovulation, intrauterine device (IUD), intrauterine hormone-releasing system ( IUS) bilateral tubal occlusion, vasectomy, and sexual abstinence. Contraception must be used until 56 days after the last infusion).

Criteria for randomisation (at year two):

-No severely reduced renal function (creatinine clearance <30 mL/min despite fluid replacement)

-No progressive bone disease diagnosed using bone imaging, less than or equal to three month prior to the randomization (year two)

-The patient should have received at least 12 infusions with zoledronic acid in the previous two years period. If a patient has received less than 12 infusions in the previous two years he / she it not eligible for randomisation and should leave the study.

Patients who fail to be included in the study will be treated according to the local standards. Patients who will be excluded from the study because they fail to meet the criteria for randomisation (at year two) will likewise be treated according to the local standards. Radiological data from these patients will still be used to evaluate secondary endpoints in the study. No additional protocol related follow-up is planned once the patients leaves the protocol either timely or untimely. Future treatment will be decided by the local hospital and the patient.

Amendment: Patients may be included when they have received two years of zoledronic acid treatment outside clinical trials. They will proceed directly to randomisation

Inclusion criteria (amendment)

- Earlier diagnosed with symptomatic Multiple Myeloma according to the IMWG criteria, regardless of bone disease status

-Signed Informed Consent

-Age ≥ 18 years

-Remaining life expectancy ≥ 1 years

-Received 23-25 monthly infusions with zoledronic acid

-Any concurrent anti-myeloma treatment are allowed

Exclusion criteria (amendment) :

-Severely reduced renal function (creatinine clearance <30 mL/min despite fluid replacement)

-Known concurrent malignancy, excluding skin cancer

-Known hypersensitivity to zoledronic acid

-Pregnant or lactating women

-Women of childbearing potential or men engaging in sexual activity with a woman of childbearing potential who refuse to use contraception (safe methods of contraception are considered to be: combined (estrogen and progestogen containing) hormonal contraception associated with inhibition of ovulation, progestogen-only hormonal contraception associated with inhibition of ovulation, intrauterine device (IUD), intrauterine hormone-releasing system ( IUS) bilateral tubal occlusion, vasectomy, and sexual abstinence. Contraception must be used until 56 days after the last infusion).

- Progressive bone disease diagnosed using bone imaging, less than or equal to three month prior to the randomization

- Developed BON during earlier zoledronic acid treatment

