**1.8 Safety Considerations and Drug administration.**

The most clinically relevant side effects to zoledronic acid include impaired renal function, hypocalcaemia, and BON. Because of this, evaluation of renal function and supplementary intake of calcium +/- vitamin D should be conducted in accordance with local guidelines. During the study, serum creatinine and ionized calcium will be measured monthly and recorded in the CRF.

Risk of BON

Concerning BON, patients should receive a thorough dental examination prior to treatment initiation if possible, maximal dental hygiene should be maintained and conservative approaches should be applied if dental problem arises. Oral investigation will be conducted at least once a year in the first two years and every 3 months from year 2 to 4 by the treating physician in order to detect any cases of BON. All cases of BON will be recorded in the CRF. All cases of BON will be reported annually to the sponsor. In case of BON, it is up to the treating physician to decide if it is in the best interest of the patient to remain on bisphosphonate treatment or if treatment should be stopped, in which case the patient is excluded from the study.

In case dental problems arise, they shall if possible be treated conservatively. No data exists as to whether zoledronic acid should be withheld or continued if tooth extraction cannot be avoided. If the treating clinician finds in the best interest of the patient, infusion with zoledronic acid may be withheld up to one month prior to tooth extraction, and up to maximum three months after tooth extraction, thus allowing a four-month pause in total from zoledronic acid treatment. It is recommended however that the patients receive prophylactic antibiotic in case tooth extraction cannot be avoided [[12](#_ENREF_12)].

Risk of PBD

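### Both routes to randomisation bar only imaging-diagnosed PBD, while the endpoint also counts hypercalcaemia, so a patient who already meets the event definition can be randomised and scored within weeks

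*Protocol*

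**What the plan says.** The primary endpoint in section 1.5 is "To compare the time to PBD from year 2 to year 4 in patients treated with monthly zoledronic acid in two consecutive years", against four years of treatment. The PBD definition in that section is a composite. Most of its components are skeletal findings, but one is a laboratory criterion: "hypercalcaemia caused by the myeloma (S-Ca-ion > 1,40 mmol/L", or an albumin-adjusted threshold if ionised calcium is not measured), "measured in at least two consecutive blood samples". The sPBD definition contains the same component.

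For entry to the randomised phase, section 1.6 (criteria for randomisation at year two) requires "No progressive bone disease diagnosed using bone imaging, less than or equal to three month prior to the randomization (year two"). Patients who enter under the amendment are excluded for "Progressive bone disease diagnosed using bone imaging, less than or equal to three month prior to the randomization".

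Section 1.5 sets one baseline rule for these endpoints: "The modality used at the time of randomisation (year 2) will be used as baseline value". Section 1.8 adds that "During the study, serum creatinine and ionized calcium will be measured monthly and recorded in the CRF".

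**The concern.** A trial of time to a first new event should start with patients who are free of that event. Here the entry criterion covers only part of the endpoint definition. Hypercalcaemia cannot be seen on a scan, so a patient can meet the PBD definition by calcium on the day of randomisation and still satisfy the criterion.

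Such an event is prevalent: neither stopping nor continuing zoledronic acid caused it. It would fall at the very start of the time-to-event curve, and would count in the primary endpoint and in the PBD and sPBD incidences. Patients who already have the event under study would also be randomised to stop or continue treatment.

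**Working it through.** **1. Does any other rule close the gap?**

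- *Other year-two criteria (1.6):* creatinine clearance and at least 12 infusions. Neither concerns calcium.
- *Other amendment exclusions (1.6):* renal function, other malignancy, hypersensitivity, pregnancy and contraception, and earlier BON. None concerns calcium.
- *Withdrawal rules (1.12):* none removes a patient for hypercalcaemia before randomisation.
- *Baseline rule (1.5):* it fixes the imaging modality. No calcium baseline is set.
- *Wording of the definition (1.5):* osteolytic lesions and vertebral compressions must be new. Hypercalcaemia need not be, and neither sample has to follow randomisation.

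The gap is open on both routes.

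**2. How soon would the event be scored?** Calcium is measured monthly. If high values persist, the second consecutive post-randomisation sample falls about 4 to 8 weeks after randomisation. If a pre-randomisation sample may serve as one of the two, the first sample afterwards is enough.

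**3. The plan's own sample size.** Inputs from section 1.13: 7.5% per year on zoledronic acid, a risk reduction of 0.5 (so 15% per year after stopping), one-sided 0.05, 80% power and two years of follow-up.

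n per group = (1.645 + 0.842)² × [1/(1 − e^−0.15) + 1/(1 − e^−0.30)] / (ln 2)², which rounds up to 143. With 20% lost before randomisation, 286/0.8 = 357.5, or 358. Both figures reproduce and are not in question.

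**4. How many patients?** The documents give no frequency of hypercalcaemia at year 2. For scale, assume that a case present at randomisation arose in the preceding two to three months, and that the 7.5% per year for all PBD components applies then:

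- two months: 286 × 0.075 × 2/12 = 3.6 patients
- three months: 286 × 0.075 × 3/12 = 5.4 patients

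These counts cover every PBD component. Myeloma hypercalcaemia with an unchanged scan is only a part of them. If that part were 10% to 30% (an assumption), the count would run from 0.1 × 3.6 = 0.4 to 0.3 × 5.4 = 1.6 patients in the whole trial.

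**5. Effect on the comparison.** Two-year risks without prevalent cases are 1 − e^−0.15 = 13.9% (arm B, continue) and 1 − e^−0.30 = 25.9% (arm A, stop). Let k patients per arm enter with hypercalcaemia and be scored. The risk in each arm becomes [(143 − k) × p + k]/143. Power is from a two-proportion comparison with 143 per arm, one-sided 0.05. The implied hazard ratio is ln(1 − risk B)/ln(1 − risk A).

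| k per arm | Risk B | Risk A | Implied HR | Power |
|---|---|---|---|---|
| 0 | 13.9% | 25.9% | 0.50 | 81.7% |
| 1 | 14.5% | 26.4% | 0.51 | 80.5% |
| 2 | 15.1% | 27.0% | 0.52 | 79.3% |
| 3 | 15.7% | 27.5% | 0.53 | 78.1% |

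The row k = 3 means six patients in total, more than the 5.4 that step 4 gives for all components together.

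**The case against.** The strongest reply is that this is rare and nearly harmless. All main-route patients are on zoledronic acid before year two. The hypercalcaemia must be caused by the myeloma, occur with an unchanged scan and persist or recur after randomisation. Randomisation should balance such patients on average. This stands, and it limits the size of the point, but it does not remove the mismatch between eligibility and endpoint.

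A second reply is that the dating of events, including whether both calcium samples must follow randomisation, is commonly left to a statistical analysis plan, which is not shown here. That stands for the dating rule. It does not help with eligibility: a dating rule alone would still let in a patient with persistent hypercalcaemia, whose next two samples would score.

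A third reply is that section 1.5 says PBD can be diagnosed on radiography or low-dose CT, which might suggest that every PBD event is an imaging event. That fails, because the same definition expressly lists a calcium threshold, which no scan can establish.

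Two stronger readings are tempting. A reader might assume that 1% to 2% of the 286 patients (3 to 6) are affected and call this 9% to 19% of the 32 events expected in section 1.13. The documents do not support it. The percentage has no source, and it roughly equals the whole PBD rate of step 4. The 32 is one year of events (143 × 0.075 + 143 × 0.15 = 32.2), whereas the endpoint spans two years, for which the same rates give about 57 (143 × 0.139 + 143 × 0.259). A reader might also infer that the bias must be towards no difference. That assumes persistence is unrelated to allocation. Arm A stops zoledronic acid, and section 1.3 itself suggests that withholding bisphosphonate may raise the risk of hypercalcaemia, so persistence could be more frequent in arm A.

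**Conclusion.** The point holds as a mismatch between the eligibility criteria and the endpoint definition, in the current text and on both routes. Followed as written, the plan can randomise a patient who already meets its own event definition and score that patient within weeks.

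The effect is small. Even three such patients per arm, more than the protocol's rates make likely, cost 3.6 percentage points of approximate power (81.7% to 78.1%); one per arm costs 1.2 points. These figures assume equal numbers in each arm, all scored as events, and the section 1.13 rates. Dilution is the main expected effect, but its direction is not certain. The point does not show that the sample size is wrong or that the primary comparison is invalid. It is worth correcting because the correction is cheap.

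**What to change.** Reconcile eligibility with the endpoint in two steps.

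(a) In section 1.6, make the year-two criterion and the amendment exclusion refer to PBD by any component of the section 1.5 definition present at randomisation, including myeloma hypercalcaemia that has not resolved. Tying this to unresolved hypercalcaemia avoids excluding patients whose earlier episode is over and who pose no prevalent-event problem.

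(b) In the PBD and sPBD definitions of section 1.5, count hypercalcaemia as an event only when both qualifying samples are taken after randomisation.

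Both are needed. Step (b) stops a pre-randomisation value from counting, and step (a) keeps persistent cases out.

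For main-route patients the cost is wording only, since "serum creatinine and ionized calcium will be measured monthly and recorded in the CRF". Amendment patients were treated outside the protocol, and their entry list in section 1.7 names imaging, bone markers, quality of life and BON investigation, but not calcium. They need two recent calcium values, from clinical records or taken at entry; a single result cannot satisfy a two-sample rule. A few patients may become ineligible.
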